#### NATURE OF THE KNOWLEDGE GAP IDENTIFIED

| Research Gap Types | Type of research gap used                                                                                                                       |
|--------------------|-------------------------------------------------------------------------------------------------------------------------------------------------|
| Knowledge Gap      | 
 
No evidence of evaluation of self-directed learning among nursing students in Indian setting.
 
 |

|                         |                                                                                                                                                                   |
|-------------------------|-------------------------------------------------------------------------------------------------------------------------------------------------------------------|
| Methodological Gap      | 
 
No RCT has been identified for evaluating impact of SDL with game-based learning
 
                                |
| Practical-knowledge Gap | 
 
There is practical knowledge gap in long term impact of game-based learning on undergraduate nursing curriculum
 
 |
| Population Gap          | 
 
No studies for evaluating effectiveness of SDL and game-based learning among nursing students in India
 
          |

#### RESEARCH QUESTIONS

Does the use of game-based learning as an innovative self-directed learning strategy improve nursing undergraduates' self-directed learning abilities in comparison to conventional learning method?

#### HYPOTHESIS

H1: The incorporation of game-based learning as an innovative self-directed learning strategy will be superior to conventional learning method in improving self-directed learning abilities among nursing undergraduates.

H2: Nursing students in game-based learning group will have higher knowledge scores than those in conventional learning group.

#### AIM

To compare the effect of the game-based learning as an innovative self-directed learning strategy with conventional self-directed learning strategy on knowledge acquisition, and self-directed learning abilities in nursing undergraduates through a randomized controlled trial.

#### OBJECTIVES

1. To assess the effect of game-based learning as an innovative self-directed learning strategy on knowledge acquisition among nursing undergraduates.
2. To assess the effect of conventional learning method on knowledge acquisition among nursing undergraduates.
3. To evaluate the effect of game-based learning as an innovative self-directed learning strategy on self-directed learning abilities among nursing undergraduates.

4. To evaluate the effect of conventional learning method on self-directed learning abilities among nursing undergraduates.
5. To compare the impact of game-based learning and conventional learning method on knowledge acquisition among nursing undergraduates after 12 weeks of intervention.
6. To determine whether game-based learning is superior to conventional learning in improving self-directed learning abilities in nursing undergraduates after 12 weeks of intervention.

## METHODS

### STUDY DESIGN

It is a prospective, randomized, controlled, data analyst-blinded, single centric superiority study with two parallel groups allocated at a 1:1 ratio and follow-up period of 12 weeks to identify the impact of self-directed learning strategy using educational games as an innovative learning method for nursing students in the experimental group compared with the conventional learning group as control.

### PARTICIPANTS, INTERVENTIONS, AND OUTCOMES

#### STUDY SETTING

This trial will be conducted at Smt. Radhikabai Meghe Memorial College of Nursing (SRMMCON), a renowned nursing college located in Sawangi (Meghe), Wardha, Maharashtra, India. SRMMCON is affiliated with the Datta Meghe Institute of Higher Education & Research (Deemed to be University) and is recognized by the Indian Nursing Council (INC) and the Maharashtra Nursing Council (MNC). It is dedicated to providing high-quality nursing education and training and offers undergraduate, postgraduate, postgraduate diplomas and doctoral program in nursing.

#### ELIGIBILITY CRITERIA

##### **Inclusion criteria:**

1. Participants must have been enrolled in an accredited undergraduate nursing program (B.Sc. Nursing).
2. Participants in their first or second year of study, who are most likely equipped with basic nursing knowledge but are still improving their clinical skills and self-directed learning (SDL) routines.

3. Participants who give informed consent and show a willingness to take part in the study.
4. Participants should have basic proficiency in English language, as SDL materials and assessments is in English language.
5. Participants must have access to a computer or laptop or tablet or smart phone, and internet connectivity, as SDL strategies rely on online resources and e-learning platforms.

#### **Exclusion criteria:**

1. Students who have received previous classes or training in antimicrobial resistance, antimicrobial stewardship and infection control should be excluded to prevent any potential influence on the intervention's outcomes.
2. Students who have a record of irregular attendance in class, as SDL requires dedication and regularity.
3. Students who continuously fail to engage in intervention or express a desire to withdraw can be removed from the study.

---

#### **SAMPLE SIZE**

The study hypothesize that the self-directed learning abilities and knowledge acquisition among participants attending the game based learning would be superior to those attending the conventional learning. The sample size is determined using G\*Power (Version 3.1.9.7). Assuming a significance level of 0.05 and effect size of 0.5 (based on meta-analysis study\* which estimated a medium effect size in favor of game-based learning over learning without gamification), 64 participants per arm will be required to achieve a statistical power of 80%. Considering a dropout rate of 10%, 70 participants per arm, 140 participants in total, is required.

- Census sampling will be done to eliminate the selection bias. All the basic Bsc.Nursing students from two semester will be enrolled in study with hundred in each experimental and control group. Total 200 students is planned to be enrolled.

---

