#### **RECRUITMENT**

The accessible population for this study is undergraduate nursing students at Smt. Radhikabai Meghe Memorial College of Nursing (SRMMCON), specifically first, second, and third semester students. The total accessible population consists of 200 students, with 100 students in each first and third semester. To ensure equal representation, stratified random

sampling will be used. The population will be divided into strata based on semester and 70 students will be randomly selected from each stratum. Each eligible student will be assigned a unique identification number. The study will select 70 students from the first semester students' list and another 70 from the third semester students' list using a random number generator.

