#### STRATEGIES FOR PROMOTING PARTICIPANT RETENTION AND ENSURING COMPLETE FOLLOW-UP

The researcher will follow up with participants who miss sessions or show non-compliance, offering support and solutions if needed via email, WhatsApp or phone call. Participants with workload, technological issues, or personal difficulties will be offered solutions (e.g., flexibility in gaming session or SDL discussion session, technical support). Participants who deviate but do not withdraw will be included in an intention-to-treat analysis to preserve randomization integrity. Those who fail to engage or express a desire to withdraw will be removed from the study and documented with reason of withdrawal for proper interpretation of study result and impact on sample size. If attrition is high, additional participants will be randomized to fill gaps and maintain the study's statistical power.

---

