## STATISTICAL METHODS

The study will use SPSS version 21, with tests like Shapiro-wilk, skewness, and kurtosis to evaluate the normal distribution of variables. Pre-test homogeneity will be assessed using descriptive statistics, independent t-tests, chi-square tests, and Fisher's exact test. ANOVA will compare differences in SDL ability, PL competency, and knowledge between groups. Regression analysis will explore the relationship between independent variables and dependent outcomes. Differences between pre-test and post-test will be analyzed using paired t-test. All statistical analysis will be two-sided, with a p-value less than 0.05 considered statistically significant.

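### The protocol gives two sampling plans that cannot both be followed: a census of 200 students and a random draw of 140

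*Protocol*

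**What the plan says.** Four parts of the protocol bear on the sample.

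- **Sample size, calculation.** "Assuming a significance level of 0.05 and effect size of 0.5", the section finds that "64 participants per arm will be required to achieve a statistical power of 80" per cent. It then adds an allowance for loss: "Considering a dropout rate of 10%, 70 participants per arm, 140 participants in total, is required".
- **Sample size, closing bullet.** Under the label of census sampling it states: "All the basic Bsc.Nursing students from two semester will be enrolled in study with hundred in each experimental and control group". It gives 200 as the planned total.
- **Recruitment.** The accessible population is put at 200, with 100 students in the first and 100 in the third semester. Stratified random sampling is to be used, and "70 students will be randomly selected from each stratum", by random number from each semester's list. That gives 140.
- **Strategies for promoting participant retention and ensuring complete follow-up.** If attrition is high, "additional participants will be randomized to fill gaps".

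The Study design section specifies "two parallel groups allocated at a 1:1 ratio". The Statistical methods section says: "All statistical analysis will be two-sided, with a p-value less than 0.05 considered statistically significant".

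**The concern.** The Sample size and Recruitment sections are adjacent, and they give different sampling methods and different totals for the same population. They also give different reasons: the census is meant to remove selection bias, and the stratified draw is meant to represent the semesters equally. Someone starting recruitment cannot tell whether to approach every student or to draw 70 names from each list, or whether recruitment is complete at 140 or at 200.

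The replacement rule depends on the answer, because it needs students who were not taken in the first round. A secondary question is whether the allowance for dropout in the smaller design delivers the number of completers that the protocol says it needs.

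**Working it through.** **Inputs.** Standardised effect d = 0.5, alpha 0.05, power 80%, 64 per arm, dropout 10%, 70 per arm and 140 in total, planned census of 200 with 100 per arm (all Sample size). Accessible population 200, as 100 + 100, and a draw of 70 per semester (Recruitment). Allocation 1:1 (Study design). Two-sided testing (Statistical methods; the Sample size section does not state sidedness).

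**1. Reproducing the plan's 64.** For a two-sample t-test with n per arm, the noncentrality parameter is d × √(n/2) on 2n − 2 degrees of freedom. Solving for 80% power at two-sided 0.05 gives n = 63.77, rounded up to 64, where power is 80.1%. The plan's figure reproduces exactly. A one-sided test would need only 50.15, rounded up to 51, so the calculation was two-sided.

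**2. The two designs side by side.**

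| | Census (Sample size) | Random draw (Recruitment) |
|---|---|---|
| Taken from each semester of 100 | 100 | 70 |
| Total | 200 | 2 × 70 = 140 |
| Per arm at 1:1 | 100 | 70 |
| Left in the population of 200 | 200 − 200 = 0 | 200 − 140 = 60 |
| Completers per arm after 10% loss | 100 × 0.9 = 90 | 70 × 0.9 = 63 |
| Noncentrality 0.5 × √(n/2) | 0.5 × √45 = 3.354 | 0.5 × √31.5 = 2.806 |
| Power, d = 0.5, two-sided 0.05 | 91.6% | 79.5% |

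The designs differ by 60 students and by 91.6 − 79.5 = 12.1 points of power.

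**3. The replacement rule.** Under the draw, 60 students in the stated population have not been selected and could be randomised later, if eligible and willing. Under the census there are none, so the rule cannot operate within that population.

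**4. The dropout allowance.** The stated 70 matches 64 × 1.10 = 70.4 rounded down. Losing 10% of 70 leaves 63, one short of 64 in each arm. Dividing by the retained fraction gives 64/0.9 = 71.1, so 72 per arm and 144 in total. The cost of using 70 is 80.1 − 79.5 = 0.6 points of power. If 200 are enrolled, the shortfall disappears.

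**The case against.** The best defence is that 140 is the number required and 200 the number intended, so the larger figure is deliberate over-enrolment above a powered minimum. Within the Sample size section alone this works, and a target above the minimum needs no second power calculation. It fails against Recruitment, which does not describe a minimum. It describes an actual draw of 70 names from each list, and that cannot be carried out alongside a census.

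The loss of the replacement pool under a census also has limited practical effect: with 100 per arm, 36 students per arm (36%) could be lost before completers fell below 64. This stands, and it keeps the point modest. The rule would still be written into a design in which it cannot be used.

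A reader might infer three stronger things, none of which the protocol supports.

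- **That each semester forms one arm.** The census sentence, with two semesters of 100 and two arms of 100, invites this reading. The Sequence generation section rules it out: blocks of 4 and 8, 1:1, stratified by semester. The Interventions section has participants assigned by numbered envelope after the common teaching session. Semester batches are used only for that session. Splitting each semester of 100 equally also gives 100 per arm.
- **That the investigator could choose 140 or 200 after seeing results.** Selection is from class lists; consent, pretest and allocation follow. No interim look at outcomes is described, the analyst is blinded, and the replacement rule is triggered by attrition.
- **That power is undefined or the trial is underpowered.** Power can be calculated for both designs and is about 80% or more in each. The one-completer shortfall is a rounding matter.

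**Conclusion.** The contradiction is real and nothing elsewhere in the protocol resolves it: the census of 200 and the random draw of 140 cannot both be followed. The target differs by 60 students, and expected power by about 12 points (79.5% against 91.6%). The replacement rule is usable under one design and not under the other. The dropout rounding is a correct but minor addition, worth 0.6 points of power and relevant only if the smaller sample is kept.

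This should be fixed, but it does not threaten the validity of the comparison. Randomisation within semester protects the contrast between arms at either total.

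The figures assume the plan's d = 0.5, a two-sided two-sample t-test at 0.05 and exactly 10% loss in each arm. The 91.6% also assumes that all 200 students are randomised. Because the eligibility and consent criteria still apply, 200 is best read as a ceiling. The population is taken as the 200 that Recruitment totals. That section also names the second semester but counts no students for it.

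**What to change.** Keep one design and delete the text of the other.

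- **If the census is kept:** remove the selection of 70 per semester from Recruitment. State that all eligible, consenting students of the two semesters, at most 200, are randomised 1:1 within semester as Sequence generation already provides. Add that 200 randomised with 10% dropout leaves 90 completers per arm and about 92% power for d = 0.5. Remove the replacement rule from the retention section, or reconcile it with a design that leaves no reserve.
- **If the random sample is kept:** delete the census bullet from Sample size. Then either state that 70 per arm with 10% dropout leaves 63 completers and 79.5% power, or raise the target to 72 per arm, 144 in total, drawing 72 from each semester. The replacement rule can then draw on the students not selected: 60 at a total of 140, or 56 at 144.

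The cost is protocol wording, plus four more students if 144 is preferred to restating the power.

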#### **RECRUITMENT**

The accessible population for this study is undergraduate nursing students at Smt. Radhikabai Meghe Memorial College of Nursing (SRMMCON), specifically first, second, and third semester students. The total accessible population consists of 200 students, with 100 students in each first and third semester. To ensure equal representation, stratified random

sampling will be used. The population will be divided into strata based on semester and 70 students will be randomly selected from each stratum. Each eligible student will be assigned a unique identification number. The study will select 70 students from the first semester students' list and another 70 from the third semester students' list using a random number generator.

#### ASSIGNMENT OF INTERVENTIONS (FOR CONTROLLED TRIALS)

##### ALLOCATION

##### SEQUENCE GENERATION

Researcher will use computer-generated random numbers to allocate participants to one of the two groups. The randomization method employs block randomization with block size of 4 and 8. Stratification is based on the semester of their study, as this factor may influence the study outcome. Independent personnel not involved in the study will utilize random sequence generator software to generate a random sequence, randomly allocating subjects in a 1:1 ratio and dividing them into two groups.

##### ALLOCATION CONCEALMENT MECHANISM

Random numbers will be placed in coded, opaque envelopes and entrusted to personnel not involved in study until the random allocation and intervention is initiated.

##### BLINDING (MASKING)

An independent assessor, not involved in intervention delivery will conduct outcome assessment for an educational intervention. Due to the nature of the intervention, blinding the researcher is not possible. The data analyst will be blinded in the study. The data will be coded with neutral labels, ensuring unbiased analysis without revealing group assignments.

##### INTERVENTIONS

Researcher will provide detailed information about purpose and procedures of the study to the participants. They will be ensured for the anonymity of participants' personal information and collected data. Participants will be made aware of approximate time needed to complete the questionnaire (around 15-25mins). They will be informed that there will be no penalty for not participating and they can withdraw at any time during the study. They will be assured that their responses would not have any effect on their academic ground and it will be kept confidential with researcher. A written informed consent will be taken from the subjects willing to participate in the study.

After signing an informed consent form, participants will undertake a pretest covering knowledge, self-directed learning abilities, and perceived learning competency. Following that, two batches of students on the basis of their academic semester will participate in a 90-minute structured teaching session on self-directed learning, where the students will be

engaged in group activity and the concept of self-directed learning, its importance and process will be discussed with them.

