## OUTCOMES

The outcome measurements will be conducted at baseline, immediately postintervention, 4 weeks postintervention, and 12 weeks postintervention using the same data collection tool.

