### **Secondary Outcome:**

#### **1. Cognitive, Affective and Psychomotor perceived learning Improvement:**

Improvement in the cognitive, affective and psychomotor domain of CAP perceived learning competency scale on postintervention score of experimental group will signify positive impact of intervention.

---

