- d. Interpersonal communication: four items ( $\alpha = 0.76$ ).

The Self-directed learning instrument (SDLI) metric uses a five-point Likert scale to measure self-assessment of self-directed learning (SDL) abilities. Scores range from 1 to

5, with "strongly disagree" indicating very low level of (self-assessed) abilities, and "strongly agree" indicating high level of (self-assessed) SDL abilities. All the statements are stated positively and the total possible score ranges from 20 to 100, with higher scores indicating higher SDL abilities.

- D. **Cognitive, Affective & Psychomotor (CAP) perceived learning scale:** The study will utilize the CAP Perceived Learning Scale, a nine-item, 6-point Likert scale, developed by Rovai et al. (2009), to measure perceived cognitive, affective, and psychomotor learning in game-based and conventional learning environments. The scale is a reliable and valid tool with internal consistency of 0.79 and supported concurrent validity. It generates an overall score representing perceived learning across three domains: cognitive learning, affective learning, and psychomotor learning.

Subscale cognitive learning describes a students' ability to recall or recognition of knowledge, affective learning is the positive attitude towards the subject matter, and psychomotor learning is the capacity to perform tasks (Rovai et al., 2009). In CAP Perceived Learning Scale, statements 1,2 and 5 measures perceived cognitive learning; statement 4,6, and 9 measures perceived affective learning and statement 3, 7, and 8 measures perceived psychomotor learning. Statement two and seven are inversely scored while the other statements are scored in a standard pattern. Total scores can range from a maximum of 54 to a minimum of 0 and CAP subscale scores can range from maximum of 18 to minimum of 0. A high CAP Perceived Learning Scale score is an indicator of a keen perception of learning by students participating in the study (Rovai et al., 2009).

Self-directed learning instrument (SDLI) and CAP Perceived learning Scale will be used for the study in its original form without any modification. Participant information with personal identifiers will be stored in paper-based form in a locked filing cabinet in a secure and locked private space. To ensure accuracy and completeness, study data will be reviewed by the researcher.

---

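### The perceived-learning (CAP) pre-test has no stated object to rate, so CAP improvement in the experimental arm cannot be read as an effect of the game

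*Protocol*

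**What the plan says.** Protocol, Interventions: after consent, "participants will undertake a pretest covering knowledge, self-directed learning abilities, and perceived learning competency". The 90-minute session on self-directed learning, the allocation and the topic material all come later. The Outcomes section sets measurement at "baseline, immediately postintervention, 4 weeks postintervention, and 12 weeks postintervention using the same data collection tool".

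Protocol, Data collection methods, item D: the CAP scale is used "to measure perceived cognitive, affective, and psychomotor learning in game-based and conventional learning environments". Its subscales cover recall or recognition of knowledge, while "affective learning is the positive attitude towards the subject matter, and psychomotor learning is the capacity to perform tasks". The same section says that the SDLI and the CAP scale "will be used for the study in its original form without any modification".

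Protocol, Exclusion criteria: "Students who have received previous classes or training in antimicrobial resistance, antimicrobial stewardship and infection control should be excluded".

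Protocol, Secondary Outcome (only one is listed): improvement in the three CAP domains "on postintervention score of experimental group will signify positive impact of intervention".

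Protocol, Statistical methods: "Differences between pre-test and post-test will be analyzed using paired t-test". An ANOVA between groups also covers perceived learning. The text does not say whether it uses post-scores or change scores.

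**The concern.** A change score is meaningful when both measurements have the same object. For the knowledge test the object is a fixed set of topic questions, and for the SDLI it is the student's own learning ability. Both can be measured before and after. For CAP, the protocol defines the object as learning within the two study environments, and neither has been met at pre-test. A student then has to rate something else: the topic without having been taught it, some other course, or nursing studies in general. The protocol does not say which. After the intervention the natural object is the trial's own teaching.

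The stated success rule makes this matter. It looks at improvement in the experimental arm alone, and the paired t-test is the tool that would test it. A rise there could come from any teaching on the topic, from the self-directed learning session that both arms receive after the pre-test, or from a change in what is being rated. The report could credit the game with an effect that the control arm shows equally.

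**Working it through.** **1. What the pre/post change contains.** Write T for the rise that any teaching on the topic would give (including the shared session), R for the shift caused by rating a different object at the two times, and G for the extra effect of the game. If T and R are common to both arms:

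- mean change, experimental arm = T + R + G
- mean change, control arm = T + R
- randomised difference in post-scores = G

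The paired test in the experimental arm tests T + R + G = 0, so it can be significant with G = 0. The between-arm difference in post-scores isolates G and needs no baseline. The between-arm difference in change also has expectation G, because the pre-test precedes allocation, but it carries the baseline's noise.

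**2. The plan's own sample size.** Inputs from the Sample size section: effect size 0.5, significance level 0.05 (two-sided per Statistical methods), 80% power. The two-sample t-test gives 63.8, hence 64 per arm, with power 80.1% at 64. The stated 64 reproduces. The effect size was not set for CAP and is used below only as an illustration.

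**3. Risk of a significant rise with no game benefit.** SD of change = SD × √(2(1 − r)), assuming equal variances, with r the pre/post correlation. The standardised change is (T + R)/√(2(1 − r)), with T + R in SD units. At r = 0 and T + R = 0.5 it is 0.5/1.414 = 0.354. Chance of a significant paired test in one arm of 64, with G = 0:

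| Common rise T + R | r = 0 | r = 0.3 | r = 0.5 |
|---|---|---|---|
| 0.3 SD | 38.7% | 51.5% | 65.7% |
| 0.5 SD | 79.5% | 91.4% | 97.6% |
| 1.0 SD | over 99% | over 99% | over 99% |

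**4. Precision if CAP change were compared between arms.** Var(change)/Var(post) = 2(1 − r).

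- r = 0: ratio 2.0, standard error × √2.0 = 1.41
- r = 0.3: ratio 1.4, standard error × √1.4 = 1.18
- r = 0.5: ratio 1.0, break-even

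Power at 64 per arm for a true between-arm post-score difference of 0.5 SD:

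| r (assumed) | Change scores | Post-scores only | Post-scores, baseline as covariate |
|---|---|---|---|
| 0 | 51% | 80% | 80% |
| 0.3 | 66% | 80% | 84% |
| 0.5 | 80% | 80% | 90% |
| 0.7 | 95% | 80% | 98% |

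At r = 0, change scores would need 127 per arm for 80% power. The documents give neither r nor the size of any common rise, so both tables show ranges under assumptions.

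**The case against.** The strongest reply is that the baseline is not empty. The protocol does not reproduce the CAP items. It describes the subscales as recall, attitude and capacity, with scores that run down to 0, and an untaught student can answer on all three. That stands: a reader might infer that the pre-test has nothing to rate, and the documents do not show this. They show that the object of the rating is not stated. Recall of what, and attitude to which subject, stay open at pre-test.

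Second, participants already know ordinary classes, because the exclusion covers one topic only. This is true, but a student who rates those classes is rating a different object from the one rated afterwards. It also means that a rise is not built in: a baseline rating of a familiar course could be high, and CAP could then fall.

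Third, the ANOVA may be meant for post-scores, in which case the wider standard error never arises. This stands, and that figure is conditional. It does not rescue the one-arm success rule or the paired test.

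Fourth, a rise common to both arms does not bias a randomised comparison, and a common rise is expected on the knowledge test too. Both statements are right. The fault lies in reading the rise from one arm, and the knowledge test at least has the same object each time.

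Fifth, the protocol's Research gap analysis summarises a pilot randomised trial of augmented reality in nursing students in which perceived learning improved in both groups. That is some precedent for measuring it before and after, although the summary does not name the scale. It also illustrates the risk: perceived learning rose in both arms, and the innovative method was not judged superior for the competency studied.

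Last, a baseline score can serve as a covariate. This stands, so removing the CAP pre-test is an option and not a necessity.

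**Conclusion.** The point holds in limited form. The CAP baseline has no stated referent, so pre-to-post change is not clearly change in one quantity. The rule that improvement in the experimental arm signifies a positive impact could therefore give a wrong conclusion. With no game benefit, a 0.5 SD common rise would pass a paired test in 64 students about 80% to 98% of the time for assumed correlations of 0 to 0.5. If CAP change were compared between arms, the standard error would be 41% to 18% wider than with post-scores at assumed correlations of 0 to 0.3. There is no loss at 0.5, and change scores gain above it.

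A reader might go further and infer that CAP is an invalid measure or that the secondary outcome is lost. The documents do not support that. Post-intervention CAP scores compared between randomised arms remain interpretable whatever the baseline means. The matter concerns a secondary outcome and leaves the SDLI and knowledge pre-tests untouched.

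**What to change.** - In Secondary Outcome, define the result as the between-arm difference in post-intervention CAP score at one named follow-up time. Twelve weeks would match objectives 5 and 6.
- In Statistical methods, state that the ANOVA for perceived learning uses post-intervention scores. State also that neither CAP change scores nor the paired pre/post t-test will be used as evidence of effect.
- For the CAP pre-test, choose one of two courses. Either drop it from Interventions, Outcomes and Data collection methods, and from the pre-test homogeneity check; or keep it, state what the student is to rate, and use it only as a covariate.
- Leave the SDLI and knowledge pre-tests as they are.

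The cost is protocol wording. There would be no within-arm CAP change result. Dropping the pre-test saves nine items but loses the baseline CAP table and a possible covariate. On the figures above, that covariate is worth nothing at a correlation of 0 and about 10 percentage points of power at 0.5.
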